#### **5.6 RANDOMISATION**

##### **5.6.1 Randomisation Procedures**

**Randomisation for the trial has been suspended until further notice on account of a USM requirement from the MHRA (12th February 2018).**

**[Procedure adopted prior to USM:** Immediately after eligibility has been established, baseline questionnaires have been completed, and once written informed consent has been obtained, the women may be randomised into the trial.

The Birmingham Clinical Trials Unit will provide third part web-based randomisation with telephone back-up. Patients are entered and randomised into the trial by logging into secure online randomisation available at <https://www.trials.bham.ac.uk/UCON>. Each centre and each randomiser will be provided with a unique log-in username and password in order to randomise a patient online. The online randomisation is available 24 hours a day, 7 days a week apart from short periods of scheduled maintenance and occasional network problems. Alternatively, investigators can make one Freephone telephone call (Tel - [name]) to the randomisation service. Telephone randomisations are available Monday-Friday, 09:00-17:00.

Clinical Assessment and Randomisation Forms will be provided to investigators and may be used to collate the necessary information prior to randomisation. All eligibility related questions and data items on the Clinical Assessment and Randomisation Form will need to be answered before a trial number can be given. Only when all eligibility criteria and baseline data items have been provided will a trial number and treatment allocation be given followed by a confirmatory email sent to the randomising investigator, local Principal Investigator, local pharmacist and the research nurse.

A minimisation procedure using a computer based algorithm will be used to avoid chance imbalances in treatment allocation and the following potentially important variables:

Age:  $\leq 35$  yrs or  $> 35$  yrs

BMI:  $\leq 25$  kg/m^2 or  $> 25$  kg/m^2

Presence of any fibroid  $> 2$ cm, as determined by the ultrasound scans

Duration of symptoms:  $< 1$  year or  $\geq 1$  year

Site: Individual Site

Agreement to enter sub-study: Both/ MRI only/ Biopsy Only/ Neither and N/A

In addition, to avoid any possibility of the treatment allocation becoming too predictable, we will include a random factor within the algorithm in which for a proportion of the allocations (1 in 5) true randomisation will be implemented rather than by using the minimised allocation.]

### **5.6.2 Treatment Allocation**

**Recruitment and randomisation for the trial has been suspended until further notice on account of a USM requirement from the MHRA (12th February 2018).**

**[Procedure adopted prior to USM:** Participants will be randomised individually into the UCON trial in an equal ratio to either ulipristal acetate (UPA) or levonorgestrel releasing intrauterine system (LNG-IUS).]

**Figure 2a: Patient pathway (Sites except Royal Infirmary of Edinburgh) Following USM**

[figure not shown]

**Figure 3b: Patient pathway (Sites except Royal Infirmary of Edinburgh) Prior to USM**

[figure not shown]

**Figure 4: Patient pathway (Royal Infirmary of Edinburgh only)**

[figure not shown]

### 5.6.3 Baseline MRI for women in mechanistic sub-study (UPA)

Women opting for the mechanistic sub-study at the Royal Infirmary of Edinburgh will, have additional assessments that relate to this study only, but will otherwise complete the same study outcome as those randomised to the UPA group and be followed up in exactly the same manner. As part of the additional assessments will, where possible undergo an MRI scan during the secretory phase (second half of her cycle) of her menstrual cycle before commencing UPA (see Figure 3).

### 5.6.4 Blinding and Emergency Unblinding Procedures

As the treatments are so different in route of administration, the participants, investigators, research nurses and other attending clinicians cannot be blinded to the treatment allocation.

### 5.6.5 Stopping of treatment or Withdrawal of Study Participants

Trial treatment should continue until a woman has reached the 12 month assessment point unless:

- If randomised to UPA – current 12 week cycle of UPA may be completed (at participant's discretion), but no new UPA treatment cycle will be started (following MHRA drug alert February 2018).
- UPA treatment must be stopped if **transaminase levels are more than two times the upper limit of normal.**
- A known serious adverse reaction to UPA occurs and in the opinion of the investigator or clinically that it is medically necessary to withdraw the woman from trial treatment.
- A suspected unexpected serious adverse reaction occurs
- A participant changes mind and wishes to become pregnant
- The participant refuses to take the trial drug
- Women allocated LNG-IUS can retain the coil *in situ* for up to 5 years if they wish (depending on the product and manufacturer), and can have the coil replaced after this

**With premature cessation of trial treatment, the trial staff will make every responsible effort to obtain, and record, information about the reasons for discontinuation, any adverse events and to follow-up the women for all safety and efficacy outcomes, as appropriate.** An end of study endometrial biopsy for women discontinuing UPA treatment should be arranged after four weeks off treatment and no later than 12 weeks from cessation of treatment.

A participant may voluntarily withdraw participation in this study at any time. If a participant does not return for a scheduled visit or return a postal questionnaire, responsible attempts will be made to contact her and where possible, complete the patient reported outcome measures, and review compliance and adverse events. If a woman decides, after randomisation, she does not wish to take UPA, or wishes to have the LNG-IUS removed or wishes to withdraw from the trial for any reason (e.g. wishes to conceive or no longer interested in the research) then the woman should be strongly advised to have an end of study endometrial biopsy taken, at least four weeks after cessation of UPA. All participants wishing to withdraw from the trial will have the option of withdrawing from all aspects of the trial but may allow for continued use of data collected up to that point.

Where possible, the site and study team will aim to document the reason for withdrawing from the trial. Clear distinction will be made in the withdrawal/change of status form as to whether a participant is withdrawing from trial treatments whilst allowing further follow-up, or whether the participant refuses any follow-up. If a participant explicitly withdraws consent to have any further data recorded their decision will be respected and recorded. All communication surrounding the withdrawal or change of status will be noted in the patient's hospital records and in the trial database and no further data will be collected for that participant. For patients changing treatment but happy to allow further follow-up, the end of study ultrasound and bloods should be collected at the original intended time-point (weeks 49-57).

The target sample size of 220 patients includes a 20% loss to follow-up rate. Rates will be monitored to detect differential drop-out, which can bias clinical trial results and reduce the power of the trial to detect important differences.

#### **5.6.1 Change of Treatment following USM**

Following the USM, new cycles of UPA will not be initiated. In such instances, participants will be offered alternative options for treatment of their HMB. Stopping treatment or change to treatment must be documented on the UCON trial database using the Withdrawal/Change of Status Form (NOTE: the section regarding "Withdrawal from Trial" does not need to be completed if the woman is continuing in the trial). Change of treatment will also be collected as part of the questionnaires at standard assessment times.

## **6 INVESTIGATIONAL MEDICINAL PRODUCT(S)**

### **6.1 STUDY DRUG**

#### **6.1.1 Study Drug Identification**

The investigation medicinal products (IMPs) are ulipristal acetate and levonorgestrel-releasing intrauterine system will be used as a reference in its authorised form.

#### **6.1.2 Ulipristal acetate (Comparator)**

UPA is provided as a 5mg tablet. The trade name for UPA in the European Union is Esmya™ for treatment of uterine fibroids, and is marketed by Gedeon Richter.

#### **6.1.3 Levonorgestrel (Reference)**

The LNG-IUS is a contraceptive device that slowly releases a daily dose of 20 µg levonorgestrel into the uterine endometrium. It is a long acting reversible contraceptive preparation that requires removal and reinsertion every five years. LNG-IUS is approved for use as a contraceptive and for HMB and in the context of the current trial is manufactured by two companies. Bayer Pharma AG market their LNG-IUS under the name of Mirena™ and Actavis UK Ltd under the name of Levosert.

#### **6.1.4 Study Drug Manufacturer and Supply**

Each centre pharmacy will arrange an initial and continuing supply of ulipristal acetate and LNG-IUS through normal procurement procedures.

#### **6.1.5 Marketing Authorisation Holder**

The marketing authorisation holder for UPA (Esmya™) is Gedeon Richter (Hungary) Plc and the marketing authorisation number(s) is EU/1/12/750/001. The ATC code is G03XB02.

The marketing authorisation holder for LNG-IUS (Mirena™) is Bayer Plc and the marketing authorisation number(s) is PL00010/0547. The ATC code is G02BA03.

The marketing authorisation holder for LNG-IUS (Levosert) is Actavis UK Ltd and the marketing authorisation number(s) is PL30306/0438. The ATC code is G02BA03.

#### **6.1.6 Labelling and Packaging**

All details of trial drug supply; labelling, storage and preparation are as per the requirements of the Medicines for Human Use (Clinical Trials) Regulations 2004 and are detailed in the UCON Pharmacy Manual which is supplied to pharmacy at the time of site approval.

UPA dispensed by the pharmacy will require a trial specific label, complying with the Annex 13 of the EU Directive on Clinical Trials, 2004. Supplies of labels will be provided to the pharmacy at each participating hospital.

As LNG-IUS is not dispensed and is fitted according to the manufacturer's recommendations, so it will therefore not require trial specific labelling.

#### **6.1.6 Storage**

The UPA tablets must be kept in the blisters in the outer carton in order to protect from light. The blister packs are Alu-PVC/PE/PVDC blister and a pack may contain 28 or 84 tablets. There are no recommendations regarding temperature control of UPA, and so no specific temperature monitoring measures are required for the UCON Trial. The shelf life of UPA is 3 years.

Storage considerations are not applicable for LNG-IUS.

#### **6.1.7 Dispensing and accountability**

At randomisation, a packet of tablets will be dispensed to the woman. The pharmacist will receive notification of the name and trial number of the randomised woman and will prepare the trial treatment tablets for labelling and dispensing. The packet of UPA will contain 12 weeks' supply for use by one participant. An accountability log will be provided to record the dispensing of trial treatment.

#### **6.1.8 Summary of Product Characteristics**

The SmPC used for the reference safety information is located in the 'SmPC Reference Document' which is stored in the site file and pharmacy file.

SmPCs for each IMP can be accessed via the electronic Medicines Compendium (eMC) which contains up to date, easily accessible information about medicines licensed for use in the UK. The SmPC for each IMP and any updates during the recruitment and follow-up phase of the trial should be stored in the site file and pharmacy file.

## **6.2 DOSE AND DELIVERY OF IMPS**

### **6.2.1 UPA**

**Randomisation was suspended on 12 February 2018 on account of a USM requirement from the MHRA (12th February 2018).**

**Participants already randomised to receive UPA may complete their current 12 week course No further courses will be initiated.**

**[Procedure adopted prior to USM:** Those allocated to UPA will receive proprietary ulipristal acetate 5mg, orally, once daily.

A single tablet must be taken orally once daily with or without food, at approximately/ or as close as possible to the same time each day. The participant should start taking UPA within the first five days of starting their menstrual bleeding.

If a participant misses a dose, she should take UPA as soon as possible. If the dose was missed by more than 12 hours, the participant should not take the missed dose and simply resume the usual dosing schedule.

Women will be instructed to take UPA in 3 courses according to the following cyclical regime ( $\pm$  5 days):

1. One 5mg tablet of UPA to be taken daily for 12 weeks then stopped for 4 weeks, when light vaginal bleeding may occur (withdrawal bleed).
2. After 4 weeks off treatment, regardless of whether they experience a withdrawal bleed, they should recommence UPA 5mg daily for another 12 weeks, then stop for 4 weeks, when they will expect to have a withdrawal bleed.
3. Repeat as for treatment courses (2).

We have chosen this regime as women and their clinicians will likely prefer a regime that has only one menstrual bleed between treatment courses and thus our study will be able to provide valuable data on this aspect of UPA treatment. ]

### **6.2.2 LNG-IUS**

**Randomisation was suspended on 12 February 2018 on account of a USM requirement from the MHRA (12th February 2018).**

The fitting of the LNG-IUS should be performed by the gynaecologist during outpatient visit, or later by a GP or at a sexual/ reproductive health clinic. If LNG-IUS is fitted within seven days of the onset of menstruation or withdrawal bleeding it will provide immediate contraceptive cover, otherwise barrier methods must be used for 14 days. The LNG-IUS can remain *in situ* up to for 5 years (depending on product and its respective shelf life) and should be removed by a competent practitioner, with immediate replacement if desired.

### 6.3 DOSE CHANGES

**Participants already randomised to receive UPA may complete their current 12 week course No further courses will be initiated.**

[Procedure adopted prior to USM: Each women randomised to UPA will take UPA 5mg, orally, once daily in 3 courses according to the cyclical regime stated in section 6.2.1:

The participant should start taking UPA within the first five days of starting their menstrual bleeding. or between 4 week and weeks 5 days from coming off treatment.]

### 6.4 PARTICIPANT COMPLIANCE

#### 6.4.1 Maximising adherence of women to their allocated treatment.

We will try to avoid women not commencing the allocated treatment firstly by careful counselling with respect to childbearing intentions. Randomised women will either be provided with their UPA prescription immediately, or we will encourage women to have the LNG-IUS fitted promptly by the gynaecologist at the baseline clinic visit. To maintain adherence, women in the LNG-IUS group will be counselled to expect some disturbance to their menstrual cycle, but encouraged to persist.

#### 6.4.2 Monitoring compliance

Follow-up questionnaires will ask for self-reported compliance to the allocated treatment. We may also collect data on adherence via a text message at various time points. LNG-IUS drug compliance will be participants who have had the coil fitted within 5 weeks post-randomisation.

UPA compliance will be those participants who report in the follow-up questionnaire to have taken the drug for at least 5 days per week. UPA drug compliance may also be evaluated by 'pill-counting'.

### 6.5 SPECIAL WARNINGS AND PRECAUTIONS FOR USE FOR ULIPRISTAL ACETATE (UPA)

Five reports of serious liver injury, including four cases of hepatic failure needing liver transplantation, have been reported worldwide in women using UPA for uterine fibroids. UPA is currently under review by the European Medicines Agency and as such, precautionary measures have been implemented by the UCON Sponsor and trial to monitor for any potential risk:

- New treatment courses of UPA will not be initiated (including in women who have completed one or more treatment courses previously)
- Monthly liver function tests will be performed in women currently taking UPA

- UPA treatment will be stopped in any woman who develops transaminase levels more than 2 times the upper limit of normal. In such cases, participants will be closely monitored and referred for specialist hepatology evaluation if clinically indicated.
- Liver function tests will be repeated in all women 2 to 4 weeks after stopping UPA treatment.
- Transaminase levels will be checked in current or recent users of UPA (i.e. those who have taken UPA at least 30 days prior to 12 February 2018) who present with signs or symptoms suggestive of liver injury (such as nausea, vomiting, malaise, right hypochondrial pain, anorexia, asthenia, jaundice). If transaminase levels are more than 2 times the upper limit of normal. Such participants will be closely monitored and referred for specialist hepatology evaluation as clinically indicated.

All LFT results should be recorded on the trial database. Any abnormal LFT results identified should be recorded and if reaching seriousness criteria (as defined in section 10.1), should be reported as an SAE/SAR (as per section 10).

There is the potential for other medicinal products to affect ulipristal acetate and conversely the potential for ulipristal acetate to affect other medicinal products. For further details regarding guidance on prohibited and permitted medications please see sections 6.9.1 and 6.9.2. For guidance regarding the potential interactions with other medications please see section 6.5.3.

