## IMPORTANT NOTICE

Following an Urgent Safety Measure issued by the Co-Sponsors of the UCON trial on 12 February 2018, recruitment to the UCON trial has been suspended until further notice.

An Urgent Safety Measure was put in place following a drug alert for Ulipristal Acetate (UPA) issued on 09 February 2018 by the European Medicine Agency and the MHRA.

The following steps have been taken in line with advice from the competent authority:

1. **Trial recruitment has been suspended.** No further participants will be recruited to the UCON trial until further notice.
2. **Participants currently on a 12 week UPA cycle** should continue with their dose until the end of the 12 week cycle and undergo monthly Liver Function Tests (LFTs) with immediate effect. Subsequent cycle(s) will not be initiated.
3. **Participants currently on a 4 week stopping period** between cycles, should **not** resume UPA.
4. All participants who have **received UPA within the last 30 days** must undergo an LFT at the earliest possibility (ideally within 2 weeks).
5. For any current or recent users of UPA presenting with **signs or symptoms suggestive of liver injury** (e.g. nausea, vomiting, malaise, right hypochondrial pain, anorexia, asthenia, jaundice) – transaminase levels must be checked immediately.
6. **Treatment must be stopped if transaminase levels are more than two times the upper limit of normal** and participants are to be closely monitored and referred for specialist hepatology evaluation if clinically indicated.
7. Participants who stop treatment **should remain** on the trial and be followed up as per the trial protocol.

The protocol and associated documents have been updated to reflect these developments while the EMA review of the safety profile of UPA is ongoing.

Participants who are currently taking UPA or have received a dose in the last 30 days will be contacted by local research teams via telephone to discuss the implications of the Urgent Safety Measure and arrange for LFTs (where appropriate). Local research teams will make every attempt to contact participants by telephone, however, if unavailable, participants will be notified of the alert by letter.

UCON participants who completed UPA treatment >30 days prior to the 12 February 2018 will be contacted by letter to provide detail of the drug alert for UPA.

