## 10 ADVERSE EVENTS AND PHARMACOVIGILANCE

The Investigator is responsible for the detection and documentation of events meeting the criteria and definitions detailed below. These tasks may also be delegated to a qualified member(s) of the research team. Assessment of events may be delegated to other suitably qualified physicians in the research team who are trained in recording and reporting adverse events.

Participants will be instructed to contact their investigator at any time after randomisation if any symptoms develop. In the case of an AE, the Investigator should initiate the appropriate treatment according to their medical judgment.

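### Protocol section 6.5 defines current or recent UPA users for the symptom-triggered liver check by exposure 30 or more days old, the reverse of the Important Notice (minor, wrong as written)

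*Protocol*

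**What the plan says.** Section 6.5 of the Protocol lists the precautions added after the Urgent Safety Measure of 12 February 2018. One bullet gives the symptom-triggered check: women with signs pointing to liver injury have their transaminases measured. It identifies them as "current or recent users of UPA (i.e. those who have taken UPA at least 30 days prior to 12 February 2018".

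The Important Notice at the front of the Protocol covers the same ground:

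- Item 5 is the symptom check itself. It begins "For any current or recent users of UPA presenting with" and gives no number of days.
- Item 4 orders an early liver function test (LFT) for all who "received UPA within the last 30 days".
- The telephone paragraph reads: "Participants who are currently taking UPA or have received a dose in the last 30 days will be contacted by local research teams".
- The last paragraph sets the remaining women apart: "UCON participants who completed UPA treatment >30 days prior to the 12 February 2018 will be contacted by letter".

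The Liver Injury subsection (numbered 6.6.1) sends the reader back to 6.5 for detail.

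**The concern.** The parenthesis is introduced as an explanation of *current or recent*, yet what it describes is old exposure. A woman taking UPA today need not have taken any 30 days ago, and a woman whose only exposure ended months ago is not a recent user. The Notice makes the intended direction plain, since it uses the same date and the same 30 days to separate recent exposure from past exposure and puts the longer interval in the letter group.

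At stake is who is offered a liver check when symptoms appear. Section 6.5 is live safety text, and it is the only place where a number of days is attached to that check. The hazard it addresses is serious: the section reports five cases of serious liver injury, four of them needing transplantation. A clinician who follows the cross-reference to 6.5 and applies its definition literally could place a symptomatic woman outside the rule.

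**Working it through.** No figure in the Protocol needs reproducing. The check is a date count and a comparison of wordings.

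**Inputs**

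- Reference date: 12 February 2018 (section 6.5 and the Notice).
- Interval: 30 days (same places).
- Planned course: 12 weeks on and 4 weeks off, "One 5mg tablet of UPA to be taken daily for 12 weeks then stopped for 4 weeks" (section 6.2.1). That is 12 × 7 = 84 days on and 4 × 7 = 28 days off.

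**Cut-off date.** Twelve days back from 12 February is 31 January, and 30 − 12 = 18 further days back is 13 January 2018. Section 6.5 therefore points to UPA taken on or before 13 January. The Notice's recent group is women still on UPA or with a dose on or after 13 January.

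**Any-dose reading (the printed words).** Let f be the days from first dose to 12 February. A woman qualifies if f ≥ 30.

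- On day d of a first course, f = d − 1. She qualifies only from d = 31, so days 1 to 30 fail: 30/84 = 35.7% of the course. These are women whose first dose fell on 14 January or later.
- After a completed 84-day course stopped k days ago, f = k + 83, which is at least 84. All such women qualify.
- A woman in a second or third course on schedule began well before 13 January and qualifies.

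**Last-dose reading (needs words that are not printed).** Let s be the days from last dose to 12 February. A woman qualifies if s ≥ 30.

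- Of s = 1 to 30, only s = 30 qualifies, so 29 of 30 are left out.
- Of the 28 days of the planned break, none qualifies.

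The result also depends on whether the gloss governs both *current* and *recent* or only *recent*:

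| Gloss governs | Exposure counted | Left out on a first course | Left out, stopped 1 to 30 days ago after a full course |
|---|---|---|---|
| both words | any dose | days 1 to 30 of 84 | none |
| *recent* only | any dose | none | none |
| both words | last dose | all 84 days | 29 of 30 days |
| *recent* only | last dose | none | 29 of 30 days |

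A woman who started after 13 January and stopped early, off schedule, would be left out in every row.

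**The two wordings are not exact opposites.** A current user who began on or before 13 January meets both the printed words of 6.5 and the Notice. In all four rows 6.5 also takes in the women whom the Notice places in the letter group. That only widens the check and harms no one.

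**The case against.** The strongest reply is that little turns on this. Three parts of it stand.

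First, the Protocol has other safeguards. Item 5 of the Notice states the symptom check without the faulty gloss. Item 2 gives current users monthly LFTs at once, and section 6.5 repeats this. Item 4 requires a test, ideally within two weeks, for everyone dosed in the last 30 days whether or not she has symptoms; that covers both early first-course users and women who have just stopped. Section 6.5 adds: "Liver function tests will be repeated in all women 2 to 4 weeks after stopping UPA treatment". Section 10 adds: "Participants will be instructed to contact their investigator at any time after randomisation if any symptoms develop".

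Second, an investigator is unlikely to use a clarifying parenthesis to exclude current users from a rule about current users.

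Third, the error has no bearing on randomisation, sample size or analysis.

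A reader might go further and infer that 6.5 removes the check from nearly all women who had recently stopped, including everyone on the planned break. The document does not support that. Section 6.5 speaks of women who have taken UPA, not of when they last took it. Where the Protocol means the end of exposure, as for the letter group, it says that treatment was completed. The figures of 29 in 30 and the whole break therefore rest on an added word.

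A reader might also infer an unprotected gap in the first 13 days after stopping, before the post-treatment LFT window opens at day 14. For women already off UPA on 12 February this does not follow: Protocol version 5 is dated 26 February 2018, 14 days later, so they were at least 15 days past their last dose by then, and the Notice tells women on a break not to resume.

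None of this makes the parenthesis correct. Scheduled tests do not replace a check prompted by symptoms, and a safety section should not depend on the reader discounting its own definition.

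**Conclusion.** The point holds as a minor error, wrong as written. Section 6.5 defines recent exposure in the reverse direction to the Important Notice.

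On the printed words the most it leaves out is women whose UPA use all began after 13 January 2018. For women following the planned schedule, that means days 1 to 30 of a first course (30 of 84 days), and only if the gloss is taken to govern *current* as well as *recent*. If it governs *recent* alone, no one on schedule is left out. Recently stopped women who had completed a course fall outside only if last dose is read into the sentence.

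The counts assume the 84-day course and 28-day break of section 6.2.1 and exposure measured at 12 February 2018. The Protocol does not say how many women were on UPA or recently off it on that date, so the number affected cannot be given. Because of the other safeguards in the Notice and in sections 6.5 and 10, the practical risk is small.

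**What to change.** The simplest change is to delete the parenthesis in section 6.5, so that its symptom check reads as item 5 of the Notice does, for current or recent users with no day count.

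If a definition is wanted, replace it with: *including all women taking UPA on or after 12 February 2018 or who took it within the 30 days before that date*. The word *including* matters. Item 5 sets no time limit on the symptom check, and the 30-day window in the Notice belongs to other actions (the early LFT and the telephone call). A replacement that confined the check to those 30 days would shut out a symptomatic woman who stopped earlier, whom item 5 does not clearly exclude.

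The cost is one parenthesis. No test, visit or form is added.
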